#### Patient-reported outcomes

For the patient-reported outcomes (e.g. HRQOL, prostate-specific anxiety, etc.) we will compare changes in mean questionnaire scores over time between the usual care and the intervention group. Based on 390 patients and a survey attrition of 20%, power is at least 80% to detect a difference in questionnaire-based outcomes between patients who had their follow-up at their GP or specialist with an effect size of 0.1, at a two sided-significance level of 5%. With this sample size we will be able to detect clinically meaningful differences [53].

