### Randomization

In total, 390 consenting men will be randomized to either the GP-based (*n* = 195) or specialist-based (n = 195) follow-up care group. Randomization will be on a 1:1 ratio. The minimization technique will be applied using a randomization program (ALEA, FormVision, Abcoude, the Netherlands) to balance usual care with the intervention within a hospital on type of primary treatment (prostatectomy or radiotherapy) and clinical stage (according to the European Association of Urology (EAU) risk scores: low risk; intermediate risk; high risk [10]). Blinding of participants and clinicians is not possible due to the nature of the intervention.

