### Power calculation

A total of 390 patients will be entered in this trial, 195 patients in each arm. Based on the objectives, the sample size is calculated separately for patients treated with prostatectomy (*n* = 270) and patients treated with radiotherapy (*n* = 120).

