#### The management of treatment-related side effects as experienced by patients

With a sample of 120 patients who have been treated with radiotherapy, we are able to test the management of treatment-related side effects as experienced by patients. Hence, we will focus on questions from three scales of the “Assessment of Patients’ Experience of Cancer Care (APECC) survey” (information exchange; physicians’ affective behavior; and physicians’ knowledge) [44]. We will use the mean score of those three scales to measure patient satisfaction with the follow-up care. Arora and colleagues observed SDs between 15.8 and 24.9 for these three scales [44]. We assume that these SDs are generalizable to our hospital patient group. For a SD of 15.8, power is 80% to detect a clinically relevant difference of 8.1 points (effect size = 8.1/15.8 = .51) with 60 patients in each group (two-sided alpha 5%) [53].

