#### Secondary study outcomes

For patients treated with prostatectomy, time from a BCR to prostate cancer retreatment decision-making will be evaluated by Kaplan-Meier methods including log-rank tests as well as multivariable Cox proportional hazards regression. Non-proportionality of hazards will be assessed by Schoenfeld residuals. In exploratory analyses, we will perform subgroup analyses by patient characteristics (e.g.: clinical stage: ≤ cT2b-c or cT3).

Scores for the APECC, EORTC QLQ-C30 and QLQ-PR25, MAX-PC, NCQ, EQ-5D-5L questionnaires will be calculated according to published scoring algorithms. Between-group differences over time in mean scores will be tested using a mixed effects modelling approach. For the moderation analysis, a regression based model will be constructed for each potential moderator separately in order to estimate the conditional (interaction) effect. Standardized effect sizes will be calculated by dividing the difference in mean change scores from baseline to follow-up between groups by the pooled baseline standard deviation.

The cost-effectiveness analysis will compare the costs and health benefits between both groups. This comparison is typically expressed in incremental cost, − health effects (often quality-adjusted life-years or QALYs), and - cost-effectiveness ratio (ICER) (e.g., incremental cost per QALY gained). A societal perspective from the Netherlands, plus lifelong time horizon will be adopted, according to the Dutch guidelines [54]. A trial-based analysis will be combined with a Markov decision analytic model, in order to capture both the trial endpoints at 2 years follow-up as well as the life long time horizon. Using a monthly cycle length, the model will simulate the lifelong course of events in a hypothetical cohort of prostate cancer survivors. We will include the estimation of the degree of uncertainty about each input parameter and the use of (probabilistic) sensitivity analyses. We will apply the most relevant severity-based ceiling ratio between €20,000 and €80,000 per QALY [55]. If necessary, Value of Information (VOI) analysis will be performed to support decision-making regarding adoption and further research [56].

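### At least 80% power at an effect size of 0.1 for patient-reported outcomes is not met on the standardised-difference scale the protocol uses, so the figure is either wrong or mislabelled

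*Protocol article*

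**What the plan says.** In the protocol article, under Power calculation (Patient-reported outcomes), the comparison is of change in mean questionnaire scores between arms. The claim is "Based on 390 patients and a survey attrition of 20%, power is at least 80" per cent, "with an effect size of 0.1, at a two sided-significance level of 5" per cent. The next sentence adds that clinically meaningful differences can be detected. No effect-size metric, within-patient correlation or number of measurements is given.

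Two other places show what effect size means in this article:

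- The power paragraph just before it, on management of side effects: "power is 80% to detect a clinically relevant difference of 8.1 points (effect size = 8.1/15.8 = .51". This is a difference divided by an SD.
- Data analysis, Secondary study outcomes: standardised effect sizes for the questionnaires will be obtained by "dividing the difference in mean change scores from baseline to follow-up between groups by the pooled baseline standard deviation". This is also a difference divided by an SD.

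On numbers: "A total of 390 patients will be entered in this trial, 195 patients in each arm", and "Randomization will be on a 1:1 ratio". Most questionnaires are collected at T0, T1, T2 and T3. Continuity of care is collected at T2 only.

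**The concern.** A standardised difference of 0.1 is small, and detecting it with 80% power normally takes well over a thousand patients per arm. The neighbouring paragraph needs 60 per group to detect 0.51. Going from 60 to 156 per arm cannot bring the detectable effect down to a fifth of that without a very strong gain from repeated measures, and the article states none.

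This matters because the article hypothesises that GP-based care is as effective as specialist care on quality of life and anxiety, yet gives no non-inferiority margin for these outcomes. The power sentence is then the only planned statement of how sensitive the trial is to differences in them. A reader who takes 0.1 on the reporting scale will credit the trial with much more sensitivity than it has.

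**Working it through.** **Inputs from the article.** 390 randomised 1:1; 20% attrition, so 390 × 0.8 = 312 evaluable, 156 per arm; two-sided alpha 5%; effect size 0.1; claimed power at least 80%.

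**Assumptions.** The article gives no within-patient correlation r. I use 0.5-0.7 as the central range and 0.3-0.8 as the wider one, with equal SDs and equal correlation between all time points.

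**Step 1: which scale the power section uses.** For the side-effects paragraph, 60 per group and 8.1/15.8 = 0.513: power = Φ(0.513 × √(60/2) − 1.960) = Φ(2.808 − 1.960) = 80.2% (79.5% by t-test). The stated 80% reproduces, so that paragraph works in difference/SD units.

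**Step 2: the stated figure on that scale.** Power = Φ(0.1 × √(156/2) − 1.960) = Φ(0.883 − 1.960) = 14.1% (noncentral t: 14.2%). The claimed 80% is not reproduced. With no attrition (195 per arm) it is 16.5%; one-sided it is 22.3%.

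**Step 3: more efficient analyses.** Each analysis multiplies the SD by a factor s. Power = Φ(0.883/s − 1.960). The difference detectable with 80% power is (1.960 + 0.842) × √(2/156) × s = 0.317 × s.

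| Analysis | s | Power at 0.1, r = 0.3 / 0.5 / 0.7 / 0.8 | Detectable SD, r = 0.5 / 0.7 |
|---|---|---|---|
| Single time point | 1 | 14% at any r | 0.317 |
| Change score | √(2(1 − r)) | 11 / 14 / 21 / 29% | 0.317 / 0.246 |
| One follow-up, baseline-adjusted | √(1 − r²) | 15 / 17 / 23 / 31% | 0.275 / 0.227 |
| Mean of T1-T3, baseline-adjusted | √((1 + 2r)/3 − r²) | 26 / 28 / 35 / 46% | 0.205 / 0.177 |

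Continuity of care is measured once, so only the first row applies to it.

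**Step 4: what 80% at 0.1 would take.** s must fall to 0.1/0.317 = 0.315. That needs r = 1 − 0.315²/2 = 0.95 for a change score, √(1 − 0.315²) = 0.95 for one adjusted follow-up, and 0.92 for the adjusted mean of three. Without any such gain, n = 2 × (1.960 + 0.842)²/0.1² gives 1,570 evaluable per arm, or 3,140/0.8 = 3,925 randomised.

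**Step 5: a reading that does reproduce.** Take 0.1 as Cohen's f for a group-by-time interaction over four time points. The noncentrality is 312 × 4 × 0.1²/(1 − r), which is 12.48 at r = 0, 17.83 at r = 0.3 and 24.96 at r = 0.5, on 3 and 310 × 3 = 930 degrees of freedom. Power is 85%, 96% and 99%.

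In SD units, with two time points and a difference D in change, f = D/4, so f = 0.1 means D = 0.4 SD. With four time points, no difference at T0 and a constant D at T1-T3, f = D√3/8 = 0.217D, so D is about 0.46 SD.

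**The case against.** The strongest reply is that Step 5 may be what was done. The article powers change over time between arms, most questionnaires have four time points, and a mixed model is planned. Read as Cohen's f, at least 80% holds at every non-negative correlation. The implied 0.4-0.5 SD also sits naturally beside the 0.51 used for side effects and the remark about clinically meaningful differences. The reporting definition under Data analysis does not refer back to the power sentence either.

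Most of this stands as an explanation of how the number could have arisen. A reader might therefore infer too much from the 14%: that an arithmetic error has been proved. The documents do not support that, because the metric behind 0.1 is never named. Nor can the f reading be dismissed on the ground that f = 0.1 (d = 0.2) gives only 42% at a single time point, since that is not the comparison described.

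The reply does not rescue the sentence, however. No such metric appears in the article, and both places that show what effect size means use a difference over an SD. On the f reading, the printed 0.1 is four to five times smaller than the difference it stands for on the reporting scale.

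Two further inferences also go too far. One is that the trial is too small: the sample size is set in the prostatectomy and radiotherapy calculations, and 156 per arm gives about 94% power for 0.4 SD even in the simplest comparison. The other is that a null result would count as excluding 0.1 SD: no such margin is set, and exclusion would be judged from confidence intervals.

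**Conclusion.** The concern holds as a wrong or mislabelled power statement. On the difference/SD scale, 156 per arm gives about 14% power at 0.1 in the simple comparison and no more than about 46% in any analysis tested up to r = 0.8, against a claim of at least 80%.

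The 14% belongs with a detectable difference of 0.32 SD. The smaller detectable differences, about 0.2-0.3 SD, belong to baseline-adjusted or averaged analyses, where power at 0.1 is about 17-35% at r of 0.5-0.7. These two sets of figures should not be mixed.

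The adjusted figures rest on assumed correlations and on equal correlation across visits; the single-time-point figures do not. The failure to reach 80% does not depend on the choice of r within 0.3-0.8. The outcomes are secondary, and neither the primary comparison nor the sample size is affected.

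**What to change.** Replace the 0.1 claim with the detectable difference in baseline-SD units, the scale set for reporting under Data analysis, and name the analysis and assumed correlation for each figure. With 156 evaluable men per arm, two-sided 5% and 80% power, the options are:

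- about 0.32 SD at one time point, or for a change score at r = 0.5;
- about 0.28 SD (0.275 by the normal approximation) for one baseline-adjusted follow-up at r = 0.5;
- about 0.2 SD for the baseline-adjusted mean of T1 to T3 at r = 0.5.

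The sponsor should choose the line that matches the contrast to be taken from the mixed model, which the article does not specify. If 0.1 was meant in another metric, name it, state the contrast and correlation, and give its equivalent in SD units.

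This costs one sentence and no added patients. The stated sensitivity becomes less favourable than the text now suggests.

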### Data analysis

#### Primary study outcomes

All analyses will be performed based on the intention-to-treat principle. Analyses will first be performed to evaluate the comparability of the groups at baseline on sociodemographic and clinical variables. The percentages of patients with four PSA tests in a period of 2 years will be compared in the two arms by using chi-square tests and multivariable by logistic regression.

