**Methods:**

This multicenter, randomized, non-inferiority study will compare specialist-based (usual care) versus general practitioner-based (intervention) follow-up care of prostate cancer survivors who have completed primary treatment (prostatectomy or radiotherapy) for localized prostate cancer. Patients are being recruited from hospitals in the Netherlands, and randomly (1:1) allocated to specialist-based (*N* = 195) or general practitioner-based (*N* = 195) follow-up care. This trial will evaluate the effectiveness of primary care-based follow-up, in comparison to usual care, in terms of adherence to the prostate cancer surveillance guideline for the timing and frequency of prostate-specific antigen assessments, the time from a biochemical recurrence to retreatment decision-making, the management of treatment-related side effects, health-related quality of life, prostate cancer-related anxiety, continuity of care, and cost-effectiveness. The outcome measures will be assessed at randomization (≤6 months after treatment), and 12, 18, and 24 months after treatment.

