#### Adherence to the prostate cancer surveillance guideline and time from a BCR to prostate cancer retreatment decision making

With a sample of 270 patients who have been treated with prostatectomy, the prospective design will allow for testing of the main effect of GP-based versus specialist-based follow-up care on adherence to the prostate surveillance guideline, as represented by the timing and frequency of PSA assessments. It is expected that 90% of the patients in the usual care group will be assessed according to the guideline, defined as 4 PSA measurements in the study period of 2 years. This is in line with the observed adherence to PSA testing recommendations in a previous randomized controlled trial of shared care for follow-up of men with prostate cancer [24]. We consider an adherence percentage as low as 80% (10 percentage points non-inferiority margin) in the GP-based group as acceptable and lower adherence percentages as unacceptable. With 270 prostatectomy patients we have 86% power at a one-sided significance level of 5%.

We will also evaluate the difference between arms in time from a BCR to prostate cancer retreatment decision-making. Based on data of a retrospective cohort study of 1340 patients who were treated with prostatectomy at the Antoni van Leeuwenhoek Hospital and expert opinion, an acceptable mean time to decision-making is thought to be 30 days. We will evaluate whether the time to decision-making is substantially longer in the GP-arm than the specialist-based arm. We consider the maximally acceptable average time to decision-making in the GP-based arm as 90 days (60 days non-inferiority margin). In the absence of empirical data on the standard deviation (SD) for the time to decision-making, we assume an SD of 20 days in the specialist-arm and 60 days in the GP-arm. With 270 prostatectomy patients we expect a total of 7 patients with a BCR in each arm, which enables us to investigate the time from a BCR to prostate cancer retreatment decision making.

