## Discussion

In order to care for the needs of the increasing number of prostate cancer survivors, a more comprehensive and sustainable follow-up care model is necessary. GPs play an essential role in providing continuous and comprehensive care, and could consider the role of providing follow-up care to some cancer survivors. The evidence in the studies conducted, to date, have been limited, focusing on other cancer sites, or on shared follow-up care models. In the current study, we are evaluating a GP-based follow-up care model for men treated for localized prostate cancer (prostatectomy or radiotherapy).

It is hypothesized that GP-based follow-up care will not differ significantly with specialist-based follow-up care regarding the adherence to the prostate surveillance guideline regarding: the number of PSA measurements; the time from a BCR to prostate cancer retreatment decision-making; the management of treatment-related side effects as experienced by patients; health-related quality of life and prostate cancer-related anxiety; continuity of care and; and costs-effectiveness.

Several limitations of the trial should be noted. Prostate cancer patients will be followed up for a period of 2 years, meaning that longer-term evaluation of outcomes will not be possible. The time frame of the study is limited by the available research funding. We also recognize that not all medically eligible patients will be willing to be randomized to GP-based or specialist-based follow-up care, resulting in a study sample composed of men who have no strong preference in this regard. We will monitor the number of patients who decline to participate in the study, and the reasons for not participating, when possible.

This trial has several notable strengths, including its multicenter, randomized design, the use of an intention-to-treat strategy for the data analysis, and the inclusion of a cost-effectiveness analysis. The trial has a pragmatic character, as current practice is compared with GP-based care in the real-world healthcare system. Moreover, a process evaluation will be executed alongside this trial in order to understand and identify factors that influence GP-based follow-up care. If our trial indicates that a GP-based follow-up care is cost-effective, the process evaluation will help to describe the actual exposure to the intervention and to understand the barriers and facilitators to support effective implementation.

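### The primary comparison is designed and powered as non-inferiority with a 10-point margin, but the only analyses named for it test for a difference and do not evaluate that margin

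*Protocol article*

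**What the plan says.** The abstract sets the design: "This multicenter, randomized, non-inferiority study will compare specialist-based (usual care) versus general practitioner-based (intervention) follow-up care". The Objectives and hypotheses section repeats the non-inferiority label.

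The terms of the comparison appear in the Power calculation, under adherence to the surveillance guideline:

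- Control rate: "It is expected that 90% of the patients in the usual care group will be assessed according to the guideline", with adherence taken as four PSA measurements over the two study years.
- Margin: "We consider an adherence percentage as low as 80% (10 percentage points non-inferiority margin) in the GP-based group as acceptable". Anything lower is called unacceptable.
- Error and power: "With 270 prostatectomy patients we have 86% power at a one-sided significance level of 5" per cent.

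The analysis of this endpoint is described in one place, Data analysis, Primary study outcomes. After stating intention-to-treat, it says that the share of men with four PSA tests in two years "will be compared in the two arms by using chi-square tests and multivariable by logistic regression". It mentions no margin, no one-sided limit, no confidence interval for the difference and no rule for concluding non-inferiority. It does not restrict the comparison to prostatectomy patients.

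The Discussion restates the hypothesis for adherence and the other outcomes together: "It is hypothesized that GP-based follow-up care will not differ significantly with specialist-based follow-up care".

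**The concern.** A chi-square test of two proportions has equality as its null hypothesis. Failing to reject that null says nothing about whether a 10-point deficit has been excluded. A logistic model gives an odds ratio, which is not on the scale of an absolute margin. At the planned rates the margin corresponds to an odds ratio of (0.80/0.20)/(0.90/0.10) = 4/9 = 0.44, but at any other control rate it corresponds to a different value, and the protocol states no odds-ratio bound.

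The methods named therefore do not answer the question for which the trial was sized. The primary result is meant to inform whether PSA surveillance can move to general practice. The error to be controlled is declaring GP follow-up acceptable when adherence is in truth 10 points or more worse. The one-sided 5% in the power calculation limits that error. The 5% level of an ordinary chi-square limits a different one: declaring a difference when there is none.

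**Working it through.** **Inputs.** Control adherence 0.90, margin 0.10 (GP arm 0.80), one-sided alpha 5%, and 270 prostatectomy patients, all from the Power calculation. Allocation is 1:1 (Randomization), so n = 135 per arm. For all 390 patients, n = 195 per arm. The protocol gives no attrition for the primary endpoint, so none is assumed.

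**Step 1: reproduce the stated power.** For a non-inferiority test with unpooled variance and equal true rates of 0.90:

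- SE = sqrt(2 × 0.9 × 0.1 / 135) = 0.0365
- Power = Φ(0.10/0.0365 − 1.645) = Φ(1.094) = 86.3%

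This matches the stated 86%. In reverse, 86% power requires 134 per arm (268 in total, against 270 stated).

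**Step 2: check whether the named test could have given 86%.** A test of difference for 90% against 80% with 135 per arm has, by normal approximation, 63.5% power two-sided and 74.6% one-sided. Neither is 86%. The sample size rests on the margin-based test.

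**Step 3: compare two decision rules when the GP arm is truly at 80% and usual care at 90%.** For every pair of counts, the two binomial probabilities are multiplied, and the products are summed over the pairs that pass each rule. Write pS and pG for the observed proportions and p̄ for their mean.

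- Rule A, non-significant two-sided 5% chi-square: |pS − pG| / sqrt(2p̄(1 − p̄)/n) ≤ 1.96
- Rule B, margin test: (pS − pG) + 1.645 × sqrt(pS(1 − pS)/n + pG(1 − pG)/n) < 0.10

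| Per arm | A passes | A with continuity correction | B passes |
|---|---|---|---|
| 135 | 35.9% | 42.5% | 5.3% |
| 195 | 20.0% | 24.5% | 5.2% |

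Reading non-significance as success would raise the false-pass rate by a factor of about 35.9/5.3 = 6.8 with 135 per arm, or 20.0/5.2 = 3.8 with 195. Rule B keeps close to the planned 5%. At 90% in both arms with 135 per arm, it passes 86.3% of the time by the same enumeration, in line with Step 1.

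**Step 4: one data set.** Take 122/135 (90.4%) in usual care and 112/135 (83.0%) in the GP arm.

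- Deficit = 10/135 = 7.4 points
- Chi-square: pooled proportion 234/270 = 0.867, SE 0.0414, z = 1.79, p = 0.073
- Interval: unpooled SE 0.0411, so the 90% CI is 7.4 ± 1.645 × 4.11 = 0.6 to 14.2 points

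The chi-square shows no significant difference, yet deficits up to 14.2 points remain compatible with the data. Non-inferiority is not shown.

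**The case against.** The strongest reply is that this is a condensed article and the primary analysis gets one sentence. Margin, alpha and sidedness are fixed in the Power calculation, and the interval method and threshold are often left to a full protocol or analysis plan, which may exist. On that reading the chi-square is loose wording. Part of this stands: one cannot conclude that no margin-based analysis is planned anywhere. It does not remove the point, because the article does more than leave detail out. It names particular tests, and they conflict with its own design and power statement.

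A reader might go further and infer that the protocol adopts non-significance as its success criterion. The documents do not support that. The analysis section sets no decision rule, and the wording about not differing significantly is a Discussion sentence covering several hypotheses together. The formal objectives speak of being as effective, within a trial labelled non-inferiority. The 36% and 20% are thus the error of a reading that the text invites, not of a rule that it lays down.

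A reader might also infer the opposite harm: a GP arm within the margin being failed because the chi-square is significant. At the protocol's own rate this hardly occurs. With 90% in both arms, the chance of meeting the margin while the chi-square shows the GP arm worse is below 0.1% at either sample size.

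**Conclusion.** Wrong as written. The analyses named for the primary endpoint do not evaluate the margin that defines the trial, and the 86% power belongs to a test that the analysis section does not specify. This follows from comparing the Power calculation with the Data analysis section, and does not need the Discussion sentence.

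The size is conditional. If non-significance were read as success, false acceptance at a true 90% against 80% would be about 36% with the 270 prostatectomy patients, or 20% with all 390, instead of about 5%. Both figures are needed because the sample size is tied to prostatectomy patients while the analysis text is not. They assume an uncorrected two-sided 5% chi-square, equal arms and complete primary data.

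The point is confined to the primary endpoint. A reader might infer that the 8.1 points given for the patient-experience survey should likewise serve as a margin. The protocol powers that outcome as a two-sided test for a difference, so using it as a margin would be a new design choice.

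**What to change.** In Data analysis, Primary study outcomes:

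- Make the primary analysis the risk difference in adherence, GP minus specialist, with a valid confidence interval. Conclude non-inferiority only if the one-sided 95% lower limit, equivalently the lower end of the two-sided 90% interval, is above −10 percentage points. This matches the alpha and margin already in the power calculation.
- Keep the chi-square test as supportive.
- Report any adjusted result on the risk-difference scale so that it can be set against the margin.

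In the Discussion, reword the hypothesis on adherence in terms of non-inferiority instead of absence of a significant difference.

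The cost is wording only, with no extra patients or data. The change should be made before outcomes are compared between arms. If a full protocol or analysis plan already contains the margin-based analysis, a reference to it in the analysis section, with the rule stated, would be enough.

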## Methods/design

### Population and setting

Prostate cancer survivors who have completed primary treatment (prostatectomy or radiotherapy) for localized prostate cancer are being recruited from 12 hospitals across different regions in the Netherlands. Eligible patients are those diagnosed with invasive prostate cancer, stage cT1a–cT3; cN0–1, cM0, pNx–pN1; R0–1, who have had a prostatectomy or have completed radiotherapy (with or without androgen deprivation therapy (ADT)) as primary treatment, and are without evidence of recurrence (PSA < 0.1 ng/ml after prostatectomy or PSA < nadir+ 2.0 ng/mL after radiotherapy). Patients are excluded from the study if: they have not completed their primary treatment less than 6 months prior to randomization; are under active surveillance; are under investigation for possible recurrence; do not have a community-based GP to provide care; are actively followed by a cancer specialist for another primary cancer; are (previously) enrolled in a study requiring ongoing follow-up by a cancer specialist; have serious (treatment-related) toxicity that requires treatment; or are unable to understand the Dutch language; or do not provide written informed consent.

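### The named primary analyses ignore the minimisation factors or are on a different scale from the 10-point margin; an adjusted risk difference would fit both allocation and margin

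*Protocol article*

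**What the plan says.** Under Randomization, the article states that "The minimization technique will be applied using a randomization program", at 1:1, "to balance usual care with the intervention within a hospital on type of primary treatment (prostatectomy or radiotherapy) and clinical stage". Clinical stage there means the three EAU risk groups. Under Population and setting, patients "are being recruited from 12 hospitals across different regions in the Netherlands".

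The power section for guideline adherence sets the criterion. "It is expected that 90% of the patients in the usual care group will be assessed according to the guideline", and "We consider an adherence percentage as low as 80% (10 percentage points non-inferiority margin) in the GP-based group as acceptable". Power is stated as 86% for 270 prostatectomy patients at a one-sided 5% level.

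Under Data analysis, Primary study outcomes, the percentages with four PSA tests "will be compared in the two arms by using chi-square tests and multivariable by logistic regression". That section does not mention the margin. It also does not limit the comparison to prostatectomy patients, whereas the next section does so for time to the retreatment decision.

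**The concern.** Three parts of the plan should fit together: how patients are allocated, how the primary outcome is analysed, and the scale on which success is judged.

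- **Allocation and analysis.** Minimisation makes the arms alike on hospital, treatment type and risk group. If these predict adherence, the difference between arms varies less than under simple randomisation. An unadjusted standard error does not reflect this and is too large.
- **Margin and analysis.** The margin is a difference of 10 percentage points. A chi-square test addresses the hypothesis of no difference and yields no confidence bound. A logistic model yields an odds ratio.

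At stake are some precision and a clear reading of the result. The first error is in the safe direction: it makes non-inferiority slightly harder to show, not easier. The mismatch of scale matters more for interpretation, because neither named output answers whether adherence under GP follow-up is less than 10 points worse.

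**Working it through.** **Inputs from the article:** 270 prostatectomy patients, taken as 135 per arm at 1:1; 90% adherence in both arms; margin 0.10; one-sided 5% (z = 1.645); 12 hospitals; three risk groups. **Not in the article:** R², the share of outcome variance explained by the minimisation factors. A range is assumed.

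**1. The stated power.** SE = √(2 × 0.9 × 0.1 / 135) = 0.0365. Power = Φ(0.10/0.0365 − 1.645) = Φ(2.739 − 1.645) = 86.3%. The stated 86% is reproduced, by a formula that uses no adjustment.

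**2. Effect of ignoring the factors.** With good balance, the true sampling SD is SE × √(1 − R²).

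- Unadjusted power = Φ((0.10 − 1.645 × 0.0365) / (0.0365 × √(1 − R²)))
- Adjusted power = Φ(0.10 / (0.0365 × √(1 − R²)) − 1.645)
- Actual one-sided error of the unadjusted test = Φ(−1.645 / √(1 − R²))

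| R² (assumed) | SE too wide by | Power, unadjusted | Power, adjusted | Actual error, unadjusted |
|---|---|---|---|---|
| 0% | 0% | 86.3% | 86.3% | 5.0% |
| 2% | 1.0% | 86.5% | 86.9% | 4.8% |
| 5% | 2.6% | 86.9% | 87.8% | 4.6% |
| 10% | 5.4% | 87.6% | 89.3% | 4.2% |
| 20% | 11.8% | 88.9% | 92.2% | 3.3% |

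**3. Check by simulation.** Minimised allocation, 270 patients, 12 hospitals, three risk groups, 3,000 runs per setting; risk difference unadjusted, then adjusted by a linear model.

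| R² (about) | Power, unadjusted | Power, adjusted |
|---|---|---|
| 2.5% | 85.7% | 85.7% |
| 9% | 86.5% | 87.7% |
| 18% | 88.5% | 91.2% |

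The simulation error on each power figure is about 0.6 points (√(0.87 × 0.13 / 3000)). With true GP adherence at 80%, the unadjusted rejection rate fell from 6.1% at R² = 0 to 4.7% at about 18%. It starts above 5% because the simple normal bound is slightly liberal here. The adjusted rate was 5.2 to 5.9%, so the adjusted analysis is not conservative in the same way.

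**4. Hospital effect in one arm only.** Follow-up in the intervention arm moves to the GP, so hospital practice may act mainly in the specialist arm. The variance removed by balancing on hospital is proportional to the variance of the sum of the two arms' hospital-specific adherence rates. An effect in one arm only gives one quarter of the value for equal effects in both. R² = 10% then acts like 2.5%. The SE is too wide by 1/√0.975 − 1 = 1.3%, and power is 86.6% unadjusted against 87.0% adjusted.

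**5. Scale of the margin.** A 10-point drop corresponds to different odds ratios:

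- from 90%: (0.80/0.20) / (0.90/0.10) = 0.44
- from 85%: (0.75/0.25) / (0.85/0.15) = 0.53
- from 95%: (0.85/0.15) / (0.95/0.05) = 0.30

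No single odds ratio stands for the margin unless control adherence is fixed.

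**6. What a chi-square test would show.** As an invented result, take 122/135 adherent under specialist care and 112/135 under GP care: 90.4% against 83.0%, a difference of 7.4 points. The pooled proportion is 234/270 = 0.867, so the pooled SE is 0.0414, z = 1.79 and two-sided p = 0.07, not significant. The unpooled SE is 0.0411, so the one-sided 95% bound on the loss is 7.4 + 1.645 × 4.11 = 14.2 points. Non-inferiority is not shown, although the chi-square test finds no significant difference.

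**The case against.** The strongest case against runs as follows.

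- **A multivariable model is already planned.** A reader might infer that the primary comparison is simply an unadjusted chi-square test. The article does not support that: the same sentence names a logistic regression, and nothing says that the minimisation factors are left out of it. A covariate list and a ranking of the two analyses may properly sit in an analysis plan that is not shown. This stands, and the point does not rest on their absence.
- **No planned power is lost.** A reader might infer that the trial falls short of its stated power. It does not: 86% was calculated without adjustment, and every unadjusted figure from the formula is at or above it. If all 390 men were analysed, unadjusted power would be 95.0% by the same formula with 195 per arm. This stands.
- **The loss is conditional.** It depends on how strongly hospital and risk group predict adherence, for which the article gives no figure. In the 270 prostatectomy patients, primary treatment is constant and contributes nothing. Hospital practice may barely reach the GP arm. All of this stands and limits the size.
- **The error is conservative.** Ignoring the factors does not raise the risk of wrongly accepting GP care. This stands.

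The objection does not remove the mismatch with the margin. The article commits to two methods, and neither, as named, produces the bound on the risk difference that its criterion needs. It would also go too far to infer that non-inferiority will be claimed from a non-significant chi-square test. The article states no such rule, and its power calculation is built on the margin.

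**Conclusion.** The point holds as a modest improvement to the analysis. The chi-square test leaves out the factors used in allocation and tests a hypothesis other than the margin. The logistic model reports on a scale on which the margin is not defined.

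The efficiency cost is small. The standard error is 0 to about 5% too wide and 0 to 2 power points are forgone if the factors explain 0 to 10% of outcome variance. At 20% the loss is about 3 points. If a hospital effect worth 10% acts in the specialist arm only, it is about half a point, and if the factors do not predict adherence it is nil. These figures assume 135 per arm, 90% adherence in both arms, good balance from minimisation and the stated range of R². The planned 86% power is met either way, and validity is not in question.

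**What to change.** Make the deciding analysis a risk difference in adherence, adjusted for the minimisation factors:

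- hospital, with small hospitals pooled or hospital fitted as a random effect;
- EAU risk group;
- primary treatment, whenever both treatment groups are analysed together.

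A logistic model standardised to a risk difference would do this. Compare its one-sided 95% confidence bound with the 10-point margin. Keep the chi-square test as a descriptive result; the odds ratio can be reported beside it.

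The cost is a change of analysis wording. It needs no more patients and no new data, because the factors are already recorded for allocation. The one practical decision, how to handle small hospitals, should be fixed before outcome data are seen.
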